
### General Objective

The general objective is to reduce follow-up visits in cataract surgery patients.

### Specific Objectives

The specific objectives are (1) to compare postoperative visual outcomes after a day 0 examination in patients with either 2 follow‑up visits, one on day 7 and the other on day 30, or 1 ophthalmic follow‑up visit between day 25 and day 30; (2) to assess the safety of deferring the first follow‑up visit at 1 week; and (3) to perform a cost-benefit analysis of the intervention.

## Methods

### Study Design, Setting, and Participants

This will be a prospective, quantitative, experimental, noninferiority control study of health services use. Selected patients undergoing cataract surgery at Reiyukai Eiko Masunaga Eye Hospital irrespective of the type of surgery (SICS or phacoemulsification) will be included in the study.

All enrolled patients will undergo an examination on the first postoperative day conducted by an ophthalmologist who is unaware of the patient’s group assignment. Subsequently, the patient will proceed to the counselor’s office, where a unique identification number will be generated and the patient will be randomized into either group 1 or group 2.

In group 1, patients will be instructed to attend follow-up visits at 1 week and 1 month postoperatively. In group 2, patients will be instructed to attend a follow-up visit at 1 month postoperatively only. During the visit, the patients will receive detailed guidance on the appropriate use of medications and be educated about the signs and symptoms they should be vigilant for. The specific date of the postoperative visit will also be communicated.

At each follow-up visit, the patient will directly visit the counselor’s office. Upon arrival, they will be provided with a blank sheet of paper containing the unique identification number assigned to them on the first postoperative day. Visual acuity testing will be conducted by a blinded optometrist, while slit lamp biomicroscopy will be performed by a blinded ophthalmologist. Before leaving the hospital, the patient will return the paper to the counselor, who will then enter the necessary information into the patient’s file. 

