Limburg et al [9] investigated the benefits of postoperative follow-up in India and concluded that visual acuity at hospital discharge was not representative of visual acuity several weeks after surgery [10]. However, a study by Congdon et al [11] concluded that early vision assessment of all patients and a follow-up assessment only for patients who return to the clinic without prompting were adequate to ensure the quality of cataract surgical services. This is again countered by a study by Gupta et al [12], who presented evidence of substantial changes between visual acuity on the first postoperative day and at subsequent follow-up. Postoperative complications and uncorrected refractive errors are 2 major issues that lead to poor visual outcomes [5,13-16]. Both issues can be wholly addressed by promoting and ensuring postoperative follow-up at the designated time [17-20]. As per the National Programme of Control of Blindness, Vision 2020: Right to Sight, the recommended postoperative follow‑up visit schedule is a first follow‑up on the first postoperative day by the surgeon (mandatory), a second follow‑up between day 7 and day 10, and a third follow‑up (with refractive correction) between day 30 and day 45 [21]. Saeed et al [22] and Tinley et al [23] concluded that postoperative follow‑up visits can be safely deferred up to 2 weeks after cataract surgery, thereby enhancing the efficiency of day care units. Meltzer et al [24] performed a study using data from the PRECOG (Prospective Review of Early Cataract Outcomes and Grading) trial and reported that visual acuity immediately after cataract surgery was highly correlated with visual acuity after 40 days, suggesting that for the purposes of quality assessment, follow‑up of all patients is not needed. A study by Deshpande et al [25] concluded that visual outcomes after uneventful cataract surgery were comparable between patients followed up on days 3 to 7 and days 25 to 30 in comparison to patients directly followed up on days 25 to 30. Additionally, it was observed that the first follow‑up visit could be safely deferred until 4 weeks after uneventful cataract surgery, including phacoemulsification or small-incision cataract surgery (SICS), in patients with no preexisting ocular or systemic comorbidity [25]. The purpose of this study is to evaluate, from a safety perspective, altering the standard postoperative management guidelines after cataract surgery so that the first follow‑up visit at 1 week is deferred in patients with no significant preexisting ocular or systemic comorbidity and no intraoperative surgical complications or immediate postoperative complications at the time of discharge from the hospital.

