### Sample Size and Sampling Technique

Sample size is calculated as follows: 2[Zα + Z1 – β] 2 × (sd2/d2) = 2 [1.96 + 1.645 ] 2 × [(0.1125)2/(0.025)2] = 263 for one group, where reference mean values for postoperative visual outcomes are taken from the study conducted by Deshpande et al [25]. The number of participants in intervention group will be 263 and the number of participants in the control (reference) group will be 263. We will use a random sampling technique and computer-generated random numbers to assign patients to the intervention or control group. We generated randomized numbers with a commonly used method [26]. The assignment will be done by the counsellor on the first postoperative day. The researchers will be masked as to randomization at all postoperative visits.

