### Primary Outcome

Visual acuity measurements serve as the most important primary outcome. This includes assessing the level of visual improvement or stability achieved by patients during the 4-week follow-up period. Visual acuity outcomes can provide insights into the effectiveness of deferring follow-up visits for achieving comparable visual outcomes to the standard practice of early postoperative visits.

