## Results

More than 526 participants will be enrolled in the study, with a minimum of 263 assigned to the intervention group (deferred follow-up visits) and a minimum of 263 to the comparison group (standard practice of early postoperative follow-up visits). The sample will have diverse demographics, ensuring a representative population.

Visual acuity measurements will be obtained for both groups during the follow-up period. We will be able to statistically compute whether the deferred follow-up visit group demonstrates comparable visual acuity outcomes to the comparison group. This will be inferred if there are no statistically significant differences between the two groups in terms of visual acuity outcomes (*P*>.05).

Among the participants in the deferred follow-up visit group, the number of patients who experience postoperative complications during the 4-week follow-up period will be compared with the group with the 1-week follow up visit.

We will also determine if participants in the deferred follow-up visit group report high levels of satisfaction with the extended recovery period and reduced travel burden. The number of participants who express that deferring follow-up visits provided them with convenience and comfort during the recovery phase will be mentioned.

We will determine if reduction in early postoperative visits allows health care providers to allocate their time and expertise more efficiently, focusing on patients with immediate needs or complex postoperative care requirements.

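### The article names no analysis model, judges comparability by P>.05 and leaves final level versus improvement open; a covariate-adjusted difference in final-visit acuity, read against a margin, would settle this, with a precision gain that depends on an unstated correlation

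*Protocol article*

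**What the plan says.** Study Design, Setting, and Participants calls the trial a noninferiority study. It states that "All enrolled patients will undergo an examination on the first postoperative day" and places randomisation after that examination. Both small-incision surgery and phacoemulsification are enrolled. Acuity testing by a blinded optometrist is described for the follow-up visits; for day 1 the section mentions only an ophthalmologist's examination.

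Sample Size and Sampling Technique uses the two-sample formula for means, ending in "0.1125)2/(0.025)2] = 263 for one group". It contains no covariate term, and the SD has no stated unit.

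The outcome is described in two ways. The Abstract (Results) compares best-corrected visual acuity between the groups. Primary Outcome says "This includes assessing the level of visual improvement or stability achieved by patients during the 4-week follow-up period", and the Abstract (Methods) ties the minimum important difference to improvement on the Snellen chart.

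The Results section says "We will be able to statistically compute whether the deferred follow-up visit group demonstrates comparable visual acuity outcomes", to be inferred from "no statistically significant differences between the two groups in terms of visual acuity outcomes" (P>.05). No test, model, covariate or noninferiority margin is named. The section on data management and analysis covers only confidentiality and storage.

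On early versus late acuity, Background cites one study in which "visual acuity immediately after cataract surgery was highly correlated with visual acuity after 40 days". It also cites a study that found discharge acuity unrepresentative of acuity some weeks later, and another that found substantial change after day 1.

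**The concern.** Three elements the article does fix do not fit together.

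- **Criterion.** A non-significant difference is not evidence of noninferiority. Nothing ties the result to a margin, and imprecision makes the criterion easier to meet.
- **Variable.** A final level and a change have different variances, and the SD of 0.1125 is tied to neither. The starting point of the improvement (before surgery or day 1) is not given.
- **Unused information.** Surgery type, and day 1 acuity if it is recorded, are fixed before assignment and so are valid covariates. The sizing makes no use of them, and the text names neither for the analysis.

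At stake are a conclusion that the stated rule cannot support, and precision that could be had without more patients in a trial whose 263 per group falls short of its own formula.

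**Working it through.** **Inputs.** z values 1.96 and 1.645, SD 0.1125 and difference d = 0.025, all from Sample Size and Sampling Technique; 263 per group from the same section and from Results. The correlation r between final acuity and the covariates taken together is an assumption, because the article gives none.

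**1. The article's own figure.**
- (1.96 + 1.645)² = 12.996 and 0.1125²/0.025² = 20.25.
- With the leading factor 2, as printed: 2 × 12.996 × 20.25 = 526.3 per group.
- Without it: 12.996 × 20.25 = 263.2.

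So 263 is not what the printed formula gives; it appears only when the factor 2 is dropped. This is a separate error, and it is the source of the power gap below.

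**2. Unadjusted power at 263 per group.**
- SE = 0.1125 × √(2/263) = 0.00981.
- d/SE = 2.548, and 2.548 − 1.96 = 0.588.
- Φ(0.588) = 0.722, against the 95% implied by 1.645.

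The same figure is the noninferiority power at one-sided 0.025 if 0.025 were the margin and the true difference were zero.

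**3. Adjusted power.** Adjustment multiplies the variance by 1 − r², so SE = 0.00981 × √(1 − r²).

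| Assumed r | 1 − r² | SE | Power | 95% CI half-width (1.96 × SE) | Equivalent n per group, 263/(1 − r²) |
|---|---|---|---|---|---|
| 0 | 1.00 | 0.00981 | 72.2% | 0.019 | 263 |
| 0.3 | 0.91 | 0.00936 | 76.2% | 0.018 | 289 |
| 0.5 | 0.75 | 0.00850 | 83.7% | 0.017 | 351 |
| 0.7 | 0.51 | 0.00701 | 94.6% | 0.014 | 516 |

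The gap is about 23 points. About 4 come back at r = 0.3, about half at r = 0.5, and all of it only at r of about 0.71.

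**4. Change from a starting acuity, for comparison.** With equal variances at both times (an assumption), the variance factor is 2(1 − r).
- r = 0.3: factor 1.4, SE = 0.00981 × √1.4 = 0.01161, power Φ(0.025/0.01161 − 1.96) = Φ(0.19), about 58%.
- r = 0.5: factor 1.0, power 72%, no gain over the raw comparison.
- r = 0.7: factor 0.6, SE = 0.00760, power Φ(1.33), about 91%.

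In each case the adjusted analysis does better. With the starting value as a covariate, modelling the level or the change from that value gives the same group difference, so the choice between them no longer matters.

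**5. Effect on the P>.05 rule.** If the true difference were 0.025, the chance of P>.05 is one minus the power: about 28% unadjusted, 16% at r = 0.5 and 5% at r = 0.7. If the true difference were zero it is 95% at any precision. Under the stated rule extra precision therefore never helps to show comparability; it helps only when an interval is compared with a margin.

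**The case against.** The strongest reply is that the article does not commit to an unadjusted analysis. A P value can come from an adjusted model, an unadjusted sample-size formula does not bind the analysis, and covariates are commonly left to a full protocol or SAP, which are not shown. This stands: silence on covariates is not an error.

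It is also fair that Primary Outcome does not define a change variable. Its wording is descriptive. The ambiguity remains, because the Abstract uses both a level and an improvement.

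A reader might infer that adjustment would recover most of the lost power at no cost. The documents do not support that, for three reasons.

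- Background cites evidence in both directions on early and late acuity and gives no coefficient. A mean shift after day 1 does not by itself imply a low correlation, but nothing in the article establishes a high one. At r = 0.3 the gain is small.
- The article mentions a day 1 examination, not a day 1 acuity measurement. If acuity is not measured then, a measurement must be added.
- The contribution of surgery type cannot be sized, because neither the mix of procedures nor their difference in outcome is given.

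Finally, the shortfall from 95% to 72% belongs to the dropped factor 2, not to the absence of covariates.

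**Conclusion.** The point holds in a limited form. The article infers comparability from P>.05 in a noninferiority design and describes its primary outcome as both a level and an improvement. Those two features are in the text. That the analysis will be unadjusted is the natural reading of the formula and the rule, but it is not stated.

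A covariate-adjusted difference read against a margin resolves both features and is at least as precise for practical purposes. Its gain is conditional: from 72% to about 76%, 84% or 95% power at r of 0.3, 0.5 or 0.7. These figures rest on the article's SD and difference, on 263 analysed per group, and on an assumed r. A reader might also take adjustment as a substitute for correcting the sample size. It is not: only r of about 0.71 or more would close the gap, and no figure in the article supports that value.

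**What to change.** - Name one primary variable: best-corrected visual acuity at the final visit, in logMAR. Confirm that the SD of 0.1125 refers to this variable and unit.
- Specify a linear model of that variable on randomised group, adjusting for surgery type and, provided it is recorded before randomisation, day 1 acuity.
- State and justify a noninferiority margin. The 0.025 in the sample-size formula is not labelled as one.
- Replace the P>.05 rule: conclude noninferiority if the 95% CI of the adjusted difference excludes a deficit as large as the margin. Report the unadjusted difference as support.
- Correct the sample size separately. Do not rely on a power gain from adjustment unless a correlation is sourced.

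The cost is a few lines of analysis wording and a day 1 acuity field on the proforma and data sheet. If day 1 acuity is not already measured, one measurement is added at an existing visit; without it, the model can still adjust for surgery type alone.

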### Data Collection Technique and Tools

A proforma will be developed for data collection. A questionnaire will be prepared; counselors will ask the questions and the information will be recorded in a register. This information will be transferred to an Excel (Microsoft Corp) sheet on a daily basis.

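### The counsellor who allocates patients also transcribes the masked examiners' results into the patient's file, with no fixed fields, masked entry or source check described

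*Protocol article*

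**What the plan says.** Three sections of the article bear on this point.

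- **Allocation.** Under Study Design, Setting, and Participants, after the first-day examination "the patient will proceed to the counselor’s office, where a unique identification number will be generated and the patient will be randomized". Sample Size and Sampling Technique confirms who does it: "The assignment will be done by the counsellor on the first postoperative day".
- **Follow-up visits.** Patients report to the counsellor's office, where "they will be provided with a blank sheet of paper containing the unique identification number assigned to them on the first postoperative day". Then: "Visual acuity testing will be conducted by a blinded optometrist, while slit lamp biomicroscopy will be performed by a blinded ophthalmologist". Afterwards: "Before leaving the hospital, the patient will return the paper to the counselor, who will then enter the necessary information", and the sentence names the patient's file as the place of entry.
- **Data capture.** Data Collection Technique and Tools begins: "A proforma will be developed for data collection". It adds a questionnaire put by counsellors, a register and a daily transfer to Excel. It does not say who completes the proforma or the Excel sheet, or from which record.

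On masking beyond the two examiners, Sample Size and Sampling Technique says: "The researchers will be masked as to randomization at all postoperative visits". The counsellor is not described as masked and, having made the assignment, cannot be.

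**The concern.** Masked assessment protects a comparison only if the masked result reaches the analysis unchanged. Here the described path hands the result to the allocating role for transcription, and the sheet it arrives on has no pre-printed fields.

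Two kinds of data are exposed. Visual acuity is the primary outcome. Complications serve the second specific objective (safety of deferral), and the Results section says the numbers of patients with complications will be compared between groups. Turning a slit-lamp description into a recorded complication needs a decision about what counts. If someone who knows the arm makes that decision, the threshold can drift between arms without any intent.

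A sheet without fields also cannot distinguish a complication that was looked for and absent from one that was not written down. That weakens any complication count, even if the loss is equal in both arms.

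**Working it through.** The plan gives no figure on this point, so the check is a trace of the data path, followed by a test of whether the risk can be sized.

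**Step 1: the path as described**

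| Step | Who | Masked? | Section |
|---|---|---|---|
| ID generated, arm assigned | Counsellor | No | Study Design; Sample Size |
| ID-only sheet handed to patient | Counsellor's office | No | Study Design |
| Acuity test | Optometrist | Yes | Study Design |
| Slit-lamp examination | Ophthalmologist | Yes | Study Design |
| Sheet returned, results entered in patient's file | Counsellor | No | Study Design |
| Proforma and register completed | Not stated (counsellors ask the questions) | Not stated | Data Collection |
| Transfer to Excel | Not stated | Not stated | Data Collection |

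The fifth row is the point: an unmasked transcription step stated by the article, after two masked ones. That the examiners write their findings on the sheet is an inference, but returning it for data entry has no other evident purpose. The last two rows are open, so the trace establishes the step only as far as the patient's file.

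**Step 2: can the complication risk be sized?**

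Assume a true complication proportion p in both arms and a fraction f of events omitted in one arm only. With n = 263 per arm as stated, the apparent risk ratio is

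(n × p × (1 − f)) / (n × p) = 1 − f.

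With p = 5% and f = 20%: 263 × 0.05 = 13.2 events against 13.2 × 0.8 = 10.5, a ratio of 0.80. Both p and f are assumptions, and p cancels, so the result only restates the assumed omission. If f is 0 the ratio is 1.00; if f is 10% it is 0.90. The article supplies nothing that would fix f.

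If the same fraction is lost in both arms, the ratio stays at 1. There are then fewer events, and a real difference in proportions would shrink by the factor 1 − f.

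**Step 3: the same test for acuity**

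Assume a fraction g of records in one arm is shifted by 0.1, on the scale of the planning difference of 0.025 in the sample size formula. The mean difference moves by g × 0.1:

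- g = 2%: 0.002, and 0.002 / 0.025 = 8% of the planning difference
- g = 5%: 0.005, or 20%
- g = 10%: 0.010, or 40%

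These show what it would take to matter, not what is likely. Copying a chart value leaves little room for interpretation, so a systematic one-arm shift is much less plausible than a drifting threshold for what counts as a complication.

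**The case against.** The strongest reply has four parts.

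1. **The blank sheet is a safeguard.** It appears designed to keep the file, with its visit history, away from the examiners. This stands, and any fix must preserve it.
2. **A proforma is already planned, and a journal article condenses.** Form fields and entry rules commonly sit in a fuller document. This stands for the detail of the form. It does not dispose of the point, because the article chose to describe the step: a blank sheet, returned to the allocating role, for entry. If the proforma governs that entry, the description should say so.
3. **Acuity is a measured value.** Transcribing is not assessing, and the masked measurement exists before the counsellor sees it. This stands and confines the concern mainly to slit-lamp findings.
4. **The destination is the patient's file, not the trial data set.** This also stands. The article does not say that the Excel sheet is filled from the file.

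A reader might infer more than the text supports: that the counsellor selects at discretion what to record, that the slit-lamp findings are free text, or that the counsellor is the only person who knows the allocation. The article says that information is entered, not that it is chosen. It does not give the format of what is written. It refers to counsellors in the plural, and patients know their own visit schedule. Nor does it show that all analysis data pass through this role, or that examiner masking is thereby undone.

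**Conclusion.** The point holds in a limited form. The article describes an unmasked transcription step, by the allocating role, between masked examination and the patient's file, without fixed fields, masked entry or a source check, and without a link to its own proforma. This is a weakness in a described procedure. It is not a contradiction and not evidence that any result will be misrecorded.

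The risk is small for acuity and larger for complications. Its size cannot be estimated from the document; the figures above rest on assumed omission and shift rates and show sensitivity only. The conclusion assumes that the examiners write their findings on the returned sheet. It does not depend on whether the Excel data set draws on the file, although its consequence for the analysis does.

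The change is worth making because it is cheap and because negative findings that were never recorded cannot be recovered later.

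**What to change.** Replace the blank sheet with the planned proforma, carrying the ID only and identical at every visit, so that it reveals no more than the blank sheet does.

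- The masked optometrist records acuity in fixed fields.
- The masked ophthalmologist marks each named complication present or absent.
- The counsellor files the form unaltered, and it is kept as the source record.
- Outcome fields are entered in the data set from the form, by ID, without the allocation.

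State this path in Study Design, Setting, and Participants, and refer to it in Data Collection Technique and Tools so that the two sections describe one process.

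The cost is one printed form and about a minute more per examination, with no extra staff or procedures. It should be in place before enrolment starts. If enrolment has begun, the sheets already returned should be kept as source records.
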